Cox regression is used to estimate the conditional hazard ratio and the survival function based on longitudinal data from a dynamic cohort of individuals under surveillance for different periods. The hazard ratio estimates the magnitude of the association between chemoprophylaxis and leprosy. The measurement takes into account the different time periods that have elapsed between exposure (treatment/placebo) and the outcome (illness) for each participant until disease develops or follow-up is discontinued [20]. The survival curve will be required to handle open and continuous recruitment as well as censorship, and the survival rates can be estimated by conditional probability according to the strategy proposed by Kaplan and Meier. The statistical significance will be assessed by the Log-Rank test [21].

For all the analyses, a 5% significance level will be adopted, and 95% confidence intervals constructed for the estimates.

An interim analysis will be conducted at the end of the third year of the study to evaluate individuals who have had at least 1 year of follow-up. This analysis will verify whether the cessation of participant recruitment is warranted by the data collected thus far and will be an opportunity to revise sample calculations according to the results. Interim analysis will seek evidence of the effectiveness, or lack thereof, of chemoprophylaxis or any clear indications that the postulated effect is so unlikely that recruitment is no longer justified. The assessment will be based on the number of events accumulated thus far and the trend in the difference between comparison groups, and the discontinuation of the trial will be submitted to the Data Monitoring Committee.

The critical level of a *z* score to reject the null hypothesis in the interim analysis will be adjusted to 2.782 (*p* = 0.005) in line with the O’Brien-Fleming protocol [22]. The conservative criterion in the interim analysis protects the study from the often-misleading results obtained from smaller samples.

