### Calculation of sample size

The sample size of this study was calculated on the basis of the primary outcome of the leprosy chemoprophylaxis among contacts using rifampicin associated with BCG vaccine. For the occurrence of this outcome a minimum follow-up time was set at 1 year.

Sample size calculations were based on the proportion of contacts that would likely develop leprosy per intervention group, currently estimated at 5% for the placebo group and 2% for the rifampicin group. With an allocation ratio of 2:1, the difference of 3 percentage points, a statistical power of 80%, and a significance level of 5%, (corrected to 0.025 to account for the interim analysis), the study requires 829 participants in the intervention group and 415 controls for a total 1244 participants. Estimating a 20% loss during follow-up (based on previous ASA data), the total sample size would total 1493 participants (995 in the treatment group and 498 controls). This sample size is appropriate for the analysis of time to failure enabling the study to detect more subtle effects (hazard ratio 0.67). Assuming a 30% seropositivity for PGL-1 among controls, this sample size will provide 85% power to detect an 8 percentage point difference from the treatment group. For 2.5% LID-positive controls, the study has 77% power to detect a 2 percentage point difference. For 35% IFN-γ-based susceptibility the study has an 80% power to detect an 8 percentage point difference. The calculations were performed via PASS11 software [23].

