## Trial status

The recruitment started in July 2015; participants are currently being recruited, and we expect to close in July 2020. An interim analysis will be performed in July 2018, and the final analysis will be performed in July 2021. This is protocol version 4.

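### The interim bound of 2.782, the 5% level for every analysis and the 0.025 in the sample size do not fit together: a small overspend of alpha, a correction that was not made, and a bound that fits only near half information.

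*Protocol article*

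**What the plan says.** All quotes are from the protocol article.

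- **Level for every test (Statistical analysis):** "For all the analyses, a 5% significance level will be adopted, and 95% confidence intervals constructed for the estimates". Sidedness is not stated. The 95% intervals, and the pairing of 2.782 with p = 0.005, imply two-sided tests.
- **Interim bound (same section):** the critical z "score to reject the null hypothesis in the interim analysis will be adjusted to 2.782", described as being "in line with the O’Brien-Fleming protocol". No critical value is given for the final test.
- **Scope of the interim (same section):** the look covers contacts with at least one year of follow-up. It looks for effectiveness or its absence, considers the trend between groups, and "will be an opportunity to revise sample calculations according to the results".
- **Sample size (Calculation of sample size):** 5% versus 2%, 2:1 allocation, 80% power and a 5% level "corrected to 0.025 to account for the interim analysis", giving 829 + 415 = 1244 before losses.
- **Timetable (Trial status):** recruitment runs from July 2015 to an expected close in July 2020. "An interim analysis will be performed in July 2018, and the final analysis will be performed in July 2021".

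**The concern.** A two-look design needs one overall alpha and a matched pair of critical values. Here the interim has its own value, the blanket sentence gives 5% to everything else, and the sample-size section gives a level said to allow for the interim. An analyst following the text would test the primary outcome at 1.96 after an efficacy look at 2.782, which spends more than 5%. A final p-value of, say, 0.049 would count as significant under the text but not under a 5% design that kept 2.782.

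The bound itself is also fixed as a number, although the O'Brien-Fleming value depends on how much information is in hand, and the protocol states no information fraction. If the look comes before half the information, 2.782 makes early stopping for efficacy easier than the cited rule would. The protocol describes the criterion as conservative and as a safeguard against misleading small-sample results.

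**Working it through.** **1. Reproduce the sample size.** Inputs from Calculation of sample size: p1 = 0.05, p2 = 0.02, r = 2, power 80%. The pooled proportion is (0.05 + 2 × 0.02)/3 = 0.03. Controls needed:

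n = [z(1−α/2) √(0.03 × 0.97 × 1.5) + 0.8416 √(0.05 × 0.95 + 0.02 × 0.98/2)]² / 0.03²

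- Two-sided 0.05: (1.960 × 0.2089 + 0.8416 × 0.2394)² / 0.0009 = (0.4095 + 0.2015)² / 0.0009 = 414.7 controls, 1244.2 in total. This is the stated 415 / 829 / 1244.
- Two-sided 0.025: (2.241 × 0.2089 + 0.2015)² / 0.0009 = (0.4683 + 0.2015)² / 0.0009 = 498.4 controls, 1495.2 in total (1,497 with both arms rounded up). Power of 415 + 829 at this level is 72.4%.

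So 0.025 is numerically the one-sided form of 5%, and N contains no allowance for the interim.

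**2. Overall type I error of the two looks.** Under the null, Z1 and Z2 are bivariate normal with correlation √t, where t is the information fraction. Overall alpha = P(|Z1| > 2.782 or |Z2| > c).

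| t | final 1.96 (5%) | final 2.241 (two-sided 0.025) | final z for 5% overall after 2.782 |
|---|---|---|---|
| 0.23 | 5.38% | 2.9% | 1.994 (p = 0.046) |
| 0.40 | 5.27% | 2.8% | 1.985 (p = 0.047) |
| 0.50 | 5.21% | 2.8% | 1.979 (p = 0.048) |

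Neither stated final level gives 5% overall. One slightly exceeds it and the other is far below it.

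**3. Where 2.782 is an O'Brien-Fleming bound.** The classic two-look bounds are c/√t and c, solved for 5% overall:

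- t = 0.50: 2.797 then 1.977.
- t = 0.40: 3.110 (p = 0.0019) then 1.967 (p = 0.0492).
- 2.782 is matched at t = 0.506.

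**4. Where the interim falls.** At least one year of follow-up by July 2018 means enrolled July 2015 to July 2017. That is 2 of 5 recruitment years, so 40% of participants if accrual is even (an assumption).

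As a lower figure, those contacts have on average 2 years each: 0.4N × 2 = 0.8N person-years. The whole cohort by July 2021 has on average 3.5 years each. 0.8/3.5 = 23%, which further assumes a constant hazard.

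**5. Alpha spent at the interim.** z = 2.782 has two-sided p = 0.0054. Against the classic bound at 40%: 0.0054/0.0019 = 2.9, about three times.

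**The case against.** **The overspend is small and rests on one reading.** The excess is 0.2 to 0.4 percentage points over this range of t. The 5% sentence may be meant as the overall level, and a cited O'Brien-Fleming rule carries its own final value of about 1.97 to 1.98, which an analysis plan could supply. This stands as to size. It does not clear the text, which assigns 5% to all analyses and elsewhere states a different level as the allowance for the interim.

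**The information fraction is unknown.** The protocol gives none, and front-loaded recruitment could bring it close to one half, where 2.782 is nearly right. This stands, so the mismatch is conditional on even accrual. The 23% figure is weaker still. The Background reports an excess of cases in the first months after vaccination, and the trial is sized on proportions with a one-year minimum follow-up. The main comparison is therefore made at 40%.

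**Stronger readings that the documents do not support:**

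- *Type I error is seriously out of control.* The computed excess does not show that.
- *The bound spends about seven times too much.* That compares 2.782 with a Lan-DeMets spending bound (3.36, p = 0.0008 at 40%), which the protocol does not name.
- *The trial is undersized for its stated level.* This follows only if 0.025 is two-sided, and the stated N shows that it was not used that way.
- *Revising the sample size pushes alpha to about 6%.* Simulations give 5.8 to 6.2% under an assumed rule (80% conditional power, up to a 1.5- to 2-fold increase, unadjusted final test). With an assumed stop for low conditional power, always followed, they give 4.7 to 4.9%. The protocol states neither rule.

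**Conclusion.** The concern holds as an inconsistency in the stated levels, modest in its numerical effect.

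- **Without any timing assumption:** 1244 is the unadjusted two-sided 5% size, so describing 0.025 as a correction for the interim is wrong. Also, 2.782 followed by 1.96 exceeds 5% at every information fraction examined. The amount is about 5.2 to 5.4% for fractions from 50% down to 23%, taking the 5% sentence to cover the final primary test, as written.
- **With even accrual assumed:** the look falls at about 40% of participants, and 2.782 is looser than the classic O'Brien-Fleming bound of 3.11 by a factor of about three in alpha.
- **Left open:** a sample-size revision based on the observed difference could add inflation, but its size cannot be given without a rule.

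The text should still be corrected, because it governs the primary test and the decision on stopping recruitment, and a literal reading leads to the wrong threshold.

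**What to change.** 1. **Interim bound.** Replace the fixed 2.782 with an O'Brien-Fleming-type alpha-spending bound, two-sided 0.05 overall, evaluated at the information observed at the cut (observed over planned events).
2. **Final level.** State the matching level for the primary test in place of 5%: about 0.0497 at 40% information and 0.049 at 50% with Lan-DeMets spending. If 2.782 is kept, or the interim has already been held with it, use about 0.047 to 0.048 at 40 to 50% information (0.046 at 23%).
3. **Sample size.** Delete or relabel the 0.025, and say that 1244 is the unadjusted two-sided 5% size. At the adjusted final level the requirement is about 1,250 to 1,265 before losses. Alternatively keep 1244 and state fixed-sample power at that level as marginally below 80% (79.4% at 0.0472, 79.9% at 0.0497).
4. **Sample-size revision.** Base any revision on the pooled event rate without group comparison, or specify the rule and a final test adjusted for it.

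The cost is protocol wording, about 20 participants at most, a marginally stricter final threshold and harder early stopping for efficacy.

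### The year-3 comparative interim may be used to revise the sample size, with no limit to pooled data and two different final significance levels, so 5% error control is not assured

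*Protocol article*

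**What the plan says.** The Statistical analysis section of the protocol article gives the interim several tasks.

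- It is comparative: "Interim analysis will seek evidence of the effectiveness, or lack thereof, of chemoprophylaxis". Its basis is stated as: "The assessment will be based on the number of events accumulated thus far and the trend in the difference between comparison groups".
- In the same paragraph it "will be an opportunity to revise sample calculations according to the results".
- The only stated protection is at the interim itself: "The critical level of a *z* score to reject the null hypothesis in the interim analysis will be adjusted to 2.782", attributed to O'Brien-Fleming.
- For the primary outcome, "The statistical significance will be assessed by the Log-Rank test".
- The level is given once: "For all the analyses, a 5% significance level will be adopted, and 95% confidence intervals constructed for the estimates".

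The Calculation of sample size section states something different: the 5% level was lowered to 0.025 on account of the interim, without saying whether that is one- or two-sided. Trial status gives the timing: "An interim analysis will be performed in July 2018, and the final analysis will be performed in July 2021", with recruitment from July 2015 to July 2020.

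**The concern.** An O'Brien-Fleming boundary pays for an extra look at the data. It does not pay for choosing the final size from the treatment difference seen at that look. If the size is chosen that way and the ordinary log-rank statistic is then read against its usual critical value, that value no longer gives the nominal error. A positive result could then carry more false-positive risk than the plan states.

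The second problem is noise. The interim comes early in a trial of a rare outcome, so an effect estimated from it is a poor guide to how many contacts are needed. The same section itself remarks that small samples often mislead.

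**Working it through.** **1. The plan's own sample size.** Inputs from Calculation of sample size: 5% v 2%, 2:1 allocation, 80% power. The pooled proportion is (0.05 + 2 × 0.02)/3 = 0.03. With the pooled-variance formula, the number of controls is

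[z_α √(0.03 × 0.97 × 1.5) + 0.842 √(0.05 × 0.95 + 0.02 × 0.98/2)]² / 0.03²

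- Two-sided 5% (z = 1.960): (0.4095 + 0.2015)²/0.0009 ≈ 415, so 415 + 830 = 1245. This matches the stated 415 + 829 = 1244.
- Two-sided 0.025 (z = 2.241): (0.4683 + 0.2015)²/0.0009 ≈ 499, so 499 + 998 = 1497. This does not match.

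So 0.025 agrees with the stated size only as the one-sided form of 5%. At a two-sided 0.025 final level, 829 + 415 has 72.4% power, not 80%.

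**2. Information at the interim.** Assume uniform accrual over five years. Contacts with a year of follow-up by July 2018 entered by July 2017.

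- Interim cohort: 2/5 × 1244 = 498, or 2/5 × 1493 = 597.
- Expected events at 3% overall: 14.9 to 17.9, of about 37 planned (1244 × 0.03). The information fraction is about 0.4.
- Already enrolled by July 2018: 3/5 × 1244 = 746, or 3/5 × 1493 = 896.

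**3. Type I error with resizing.** Let t be the interim information, z₁ the interim statistic, T the revised total information (planned = 1) and c the final critical value. The trial stops if |z₁| > 2.782. Otherwise T is the smallest value in the allowed range at which conditional power on the observed trend reaches 80%, or the cap if none does:

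CP = Φ{[√t |z₁| + (|z₁|/√t)(T − t) − c√T] / √(T − t)}

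The final statistic is (√t z₁ + √(T − t) z₂)/√T. Integrating over z₁ under no effect, with t from 0.3 to 0.5, gives:

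| Rule | Final z | Two-sided error |
|---|---|---|
| No resizing | 1.96 | 5.2–5.4% |
| Increases only, cap 2–3× | 1.96 | 6.1–6.7% |
| Decreases allowed to the number already enrolled, cap 2× | 1.96 | 6.8–7.3% |
| Increase only if conditional power is 50–80% (t = 0.4–0.5) | 1.96 | 5.1–5.2% |
| Increases only, cap 2–3×, t = 0.4 | 1.985 | 5.9–6.2% |
| Increases only, cap 2–3×, t = 0.5 | 1.977 | 6.0–6.5% |
| Increases only, cap 2–3× (t = 0.4–0.5) | 2.241 | 3.4–3.6% |

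The values 1.985 and 1.977 hold about 5% when there is no resizing. The excess at those values shows that correcting the final boundary alone does not remove the problem.

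**4. Noise in the recomputed size.** The standard error of the log hazard ratio at 2:1 is √(4.5/d), which is 0.55 for 15 events and 0.50 for 18. Around a true hazard ratio of 0.40, the 95% range of the estimate is about 0.14–1.17 or 0.15–1.07.

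Interim counts were simulated at exactly 5% v 2% in 498 or 597 contacts and put through the formula in step 1. The recomputed total has a median of about 1240 and quartiles of about 690 and 2850–3330. It exceeds double the plan (2488) in about 28–30% of trials. The lower quartile is already below the 746 enrolled.

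**The case against.** Four points on the other side have force.

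- **Which results drive the revision.** The sentence does not say. The sentence about the trend describes the stopping assessment, and the event count it also names could be a pooled figure. A reader might infer that the plan orders resizing from the unblinded arm difference. That is a strong inference, because no pooled quantity is named for the revision, but the text does not say it.
- **The final level.** A reader might infer that error definitely exceeds 5%. The 0.025 in the sample-size section stands against this. As a two-sided final level it keeps error below 5% under every rule tried up to a 3× cap (worst case 4.99%). The stated size and the 5% sentence both speak against that reading, so the document is contradictory rather than settled at 1.96.
- **The rule.** No resizing rule is given, so the size of the excess depends on an assumed one. A restrained rule adds almost nothing.
- **Decreases.** A reader might infer that the trial could be cut to half or less, or that error could reach 8.5–10.8%. With 60% already enrolled by July 2018, and all randomized contacts analysed, such cuts cannot be carried out. With that floor, the worst case over all rules is about 7.1–8.1%.

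An article may also leave the detailed rule and the combination method to a fuller document. That does not dispose of the point: the article states a permission that is too broad and gives two levels that disagree.

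**Conclusion.** The concern holds in a limited form. The plan allows resizing after a comparative interim without confining it to pooled data, and its two statements of the significance level do not agree. If the arm difference is used and the final test is read at about two-sided 5%, error is about 6.1–6.7% with increases only and about 7% if decreases to the enrolled number are allowed. These figures assume uniform accrual, resizing to 80% conditional power, and caps of 2–3× and 2× respectively. This is a failure to assure 5%, not proof that 5% is exceeded.

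The noise argument does not depend on the final level. It needs only uniform accrual and the planned rates already reached in the interim cohort. Some 15–18 events cannot support a new size based on the observed effect.

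**What to change.** In the Statistical analysis section, replace the open permission with a statement such as: any revision of the sample size will use only the pooled leprosy incidence (both arms combined) and the observed loss to follow-up; the planned relative effect (2% v 5%, a risk ratio of 0.4) stays fixed, and the difference between arms is not used.

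If the sponsor does want to use the arm difference, fix the resizing rule in advance and test the final result with a pre-weighted inverse-normal combination of the log-rank statistics from before and after the interim.

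In either case, state one final significance level, with its sidedness, that agrees between the Statistical analysis and Calculation of sample size sections, and match the final critical value to the interim boundary and the actual information fraction. If a two-sided 0.025 final level is meant, the sample size has to be recalculated, since 1244 does not give 80% power at that level.

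The pooled-data option costs a sentence or two and no extra contacts or procedures. Its price is that the size can no longer adapt to the observed effect, an adaptation that so few events could not support.

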### Analyses of outcomes based on immunological and molecular parameters

The quantitative variables analyzed will be those related to the ELISA results on anti-PGL1, LID-1, and IFN-γ. The optical density (OD) of each will be read at 450 nm. PGL-1 samples with OD > 0.25 will be considered positive while LID-1 samples will be considered positive with OD > 0.3. As for IFN-γ, the reading will be performed according to the manufacturer’s recommendations (eBioscience®, San Diego, CA, USA).

Frequency distribution will be constructed to detect asymmetries and the need for scale transformation. The primary analysis will address measures of the central tendencies (mean and median), and those of dispersion (i.e., interquartile range, variance, and standard deviation).

For the continuous variables, paired measurements for each individual will result from blood samples obtained before receiving rifampicin and during the contact visit 2 months after receiving rifampicin and before receiving the BCG vaccine. The results obtained 12 months after the first blood collection will also be submitted to paired analysis with the *t* test comparing the mean values of any changes between the two groups.

The main explanatory variable is intervention (rifampicin/placebo). Bivariate and multivariate analyses (linear regression model) will consider the following major covariates: age group, bacilloscopic index (BI), and type of coexistence with the index case. The response variables will include the anti-LID-1, anti-PGL-1, and IFN-γ measurements on a continuous scale. The effect of the intervention will be evaluated and adjusted for the effects of the other explanatory variables.

Regarding the PCR results (positive/negative), bivariate and multiple analyses (logistic regression model) will include the same previously mentioned explanatory variables: age group, BI, and type of cohabitation with the index case. A 5% significance level will be adopted, and 95% confidence intervals will be constructed for the estimates. Data management will use Microsoft Access®, and statistical analyses will be conducted using SPSS version 22.0 (IBM Corp., 2013).

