After signing the forms, 16 ml of blood is collected from adults and contacts aged 12 to 17 years for the baseline identification of the following immunological markers: anti-PGL-1, anti-LID-1, and IFN-γ during the first evaluation, at the end of the second month (prior to BCG immunization), and 12 months subsequent to the initial intervention. All participants will undergo digital pulp blood sampling for rapid anti-PGL-1 testing during the initial evaluation and after 12 months following intervention. Children under 12 years of age will have only a digital pulp blood sample collected for rapid anti-PGL-1 test. This test has been validated by Bührer-Sékula et al. [10], and a simple verification of the agreement with the results of the enzyme-linked immunosorbent assay (ELISA) (anti-PGL-I) in adults will be conducted in this study to inform of the limitations of the results in children, for whom ELISA (anti-PGL-I) will not be available.

Lymph from the right earlobe is obtained by dermal scraping for DNA/ML molecular investigation (PCR) during the first evaluation, but only from the participants over 12 years of age, since children under 12 years of age are less able to bear the discomfort. Another lymph sample is collected at the end of the second month in the event the result of the first examination is either positive or inconclusive. Lymph collection follows MH guidelines, according to which the specimen is stored in a sterile bottle immersed in a 70% alcohol solution [19].

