### Statistical analysis

The evaluation of the efficacy of chemoprophylaxis will be based on the occurrence of new cases of leprosy in both groups and will be measured at least at 1 year after the single dose of rifampicin. Over the period of 1 year, three evaluations will be carried out: at baseline, 2 months, and 12 months.

The total number of randomized participants will be analyzed to preserve the safeguards against selection bias and confounding (“intention-to-treat analysis”). An alternative analytical strategy (“per-protocol analysis”) will disregard the data obtained from participants that did not meet the eligibility criteria and did not adhere to either of the intervention regimens or study procedures.

Evaluating the group that adhered to the protocol prevents classification bias that may result from analyzing the participants in the originally allocated group despite their not having followed the specifically planned procedures**.** Any discrepancies in the results of the two analytical strategies will be interpreted in light of the distribution of the baseline characteristics of the participants adhering to the protocol. The balanced distribution of covariates across comparison groups achieved by randomization could be lost as a result of violations in protocol.

The main explanatory variable defined by the study design is the intervention (rifampicin/placebo). Whereas univariate analyses will be performed to describe their baseline characteristics, bivariate analyses will explore the association between intervention and outcomes (response variables). Multivariate analyses (Cox regression) will be conducted to adjust the association estimates (hazard ratio for new cases) for covariates with any imbalance in group distribution. Subgroup analyses of effectiveness (derivatives of the measures of association) according to age, along with the BI and type of cohabitation with the index case, will be carried out.

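### The planned 12-month marker comparison is a t test on change from baseline, which omits contacts without a month-12 sample and uses the baseline and month-2 values inefficiently

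*Protocol article*

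**What the plan says.** Under Follow-up, "16 ml of blood is collected from adults and contacts aged 12 to 17 years" for the ELISA markers and IFN-γ at baseline, at month 2 before BCG, and at month 12. Children under 12 give only a finger-prick sample.

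The section on immunological and molecular parameters plans two paired comparisons for the continuous markers. The first uses "blood samples obtained before receiving rifampicin and during the contact visit 2 months after receiving rifampicin and before receiving the BCG vaccine". For the second, "The results obtained 12 months after the first blood collection will also be submitted to paired analysis", with a t test "comparing the mean values of any changes between the two groups". The same section adds regression: "Bivariate and multivariate analyses (linear regression model) will consider the following major covariates". The covariates listed are age group, bacilloscopic index and type of coexistence with the index case. Baseline marker value is not among them, and no repeated-measures structure is named.

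Two other statements bear on the point. Calculation of sample size has "Estimating a 20% loss during follow-up (based on previous ASA data", with no breakdown by visit, by arm or for blood samples. Statistical analysis states the intention-to-treat principle: "The total number of randomized participants will be analyzed to preserve the safeguards against selection bias and confounding".

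**The concern.** A within-person change from baseline to month 12 exists only for contacts bled at both visits. The test therefore works on those who came back, although most of the others will probably have a baseline and a month-2 value that say something about month 12. Two things are at stake.

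- **Precision.** Subtracting the baseline is a less efficient use of it than adjusting for it whenever the correlation between visits is below 1. The month-2 value is not used for month 12 at all.
- **Validity.** If return at month 12 depends on the month-2 marker value, and does so differently by arm, the complete pairs can show a difference that is not there. The Intervention section admits one route to differential behaviour, because the placebo does not reproduce the red colouring of urine.

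**Working it through.** **Inputs from the protocol article.** Samples at months 0, 2 and 12; 2:1 allocation; 1493 randomised; 20% loss. The article gives no precision figure for the continuous marker changes, so there is none to reproduce.

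**Assumptions (not in the article).** The 20% applies to month-12 samples, equally in both arms; everyone attends month 2; SD is 1 at each visit. Four sets of correlations are used for baseline with month 2 (r01), baseline with month 12 (r02) and month 2 with month 12 (r12). If 60–90% of participants are aged 12 or over, 20% loss removes 1493 × 0.6 × 0.2 ≈ 179 to 1493 × 0.9 × 0.2 ≈ 269 bled contacts.

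**Step 1: precision.** Large-sample variance per contact of the month-12 contrast, with losses at random:

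- Planned t test on change: A = 2(1 − r02)/0.8
- Baseline-adjusted, same contacts: B = (1 − r02²)/0.8
- Three-visit mixed model: C = (1 − r02²) × [(1 − ρ²)/0.8 + ρ²], where ρ = (r12 − r01·r02)/√[(1 − r01²)(1 − r02²)]

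| r01 / r02 / r12 | A | B | ρ² | C | B/A | C/B | C/A |
|---|---|---|---|---|---|---|---|
| 0.7 / 0.7 / 0.7 | 0.750 | 0.638 | 0.17 | 0.616 | 0.85 | 0.97 | 0.82 |
| 0.9 / 0.7 / 0.8 | 0.750 | 0.638 | 0.30 | 0.600 | 0.85 | 0.94 | 0.80 |
| 0.7 / 0.6 / 0.85 | 1.000 | 0.800 | 0.57 | 0.709 | 0.80 | 0.89 | 0.71 |
| 0.6 / 0.5 / 0.9 | 1.250 | 0.938 | 0.75 | 0.797 | 0.75 | 0.85 | 0.64 |

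Worked for the last row: ρ = (0.9 − 0.3)/√(0.64 × 0.75) = 0.866, so ρ² = 0.75, and C = 0.75 × (0.25/0.8 + 0.75) = 0.797.

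The whole gain over the planned test is 18–36% in variance (C/A), or 9–20% in standard error. Baseline adjustment alone gives 15–25% (B/A). The month-2 data then cut the remaining variance by 3–15% (C/B).

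**Step 2: how much of the dropout loss comes back.** Loss of 20% inflates the variance by 1/0.8 = 1.25. On the baseline-adjusted scale the mixed model brings this to 1.25 − 0.25ρ², so the share recovered is ρ²: 17%, 30%, 57% and 75% in the four sets. A contact who also missed month 2 contributes nothing to that recovery.

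**Step 3: bias under an adverse scenario.** Suppose there is no true difference, and in the placebo arm only, return is 95% above the median month-2 value and 74% below it. The mean month-2 value among returning placebo contacts is then 0.798 × (0.95 − 0.74)/(0.95 + 0.74) = 0.099 SD. The false difference (rifampicin minus placebo) in the change t test is −(r12 − r01) × 0.099:

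- 0.7 / 0.7 / 0.7: 0.00
- 0.9 / 0.7 / 0.8: +0.010
- 0.7 / 0.6 / 0.85: −0.015
- 0.6 / 0.5 / 0.9: −0.030

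With 900 bled contacts, the standard error of the planned contrast is √[A × (1/600 + 1/300)], which is 0.061 to 0.079 SD. The worst case is 0.030/0.079 ≈ 0.4 standard errors.

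**The case against.** The strongest case against is that this is a condensed article. The handling of missing laboratory values may sit in a fuller plan, the article never restricts the analysis to complete pairs in words, and a t test on change is a standard method. It stands that the method is not an error. But the restriction follows from the test named, so a fuller plan could avoid it only by departing from that test. Replacing a stated method by a better one is a fair comment.

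Four stronger readings are tempting and are not supported.

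- **The test contradicts intention to treat.** The principle is stated in a section that opens with new leprosy cases, and losses for that outcome are traced through the national registry. Children under 12 give no venous blood, so no analysis of these markers could include everyone randomised. At most there is some tension.
- **Month-2 values are thrown away.** They have their own comparison with baseline; they are unused only for month 12.
- **A mixed model restores the lost precision.** Step 2 shows partial recovery, which depends on attendance at month 2.
- **The planned test is materially biased.** The scenario needs return to depend on the month-2 value in one arm only. The article does not say that contacts learn their ELISA results, and the rapid test is not scheduled at month 2. Even so the bias is small.

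It also stands that the stakes are low. The listed serology outcomes concern the period before BCG, so month 12 lies outside them, although the Abstract does promise a comparison of the immunological results after 12 months.

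**Conclusion.** The point holds as a modest improvement to secondary analyses. The 12-month change t test leaves out contacts without a month-12 sample and makes inefficient use of the earlier values. A three-visit model would lower the variance of the month-12 contrast by about 18–36%, mostly through baseline adjustment. These figures rest on assumed correlations of 0.5–0.9, on applying the overall 20% loss to month-12 samples only, and on full attendance at month 2. Protection against bias is a secondary benefit: the model is valid if missingness depends only on recorded earlier values, and the planned test's bias in the scenario examined is only about +0.01 to −0.03 SD. The primary outcome is untouched.

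**What to change.** For each continuous marker, transformed if its distribution requires it, replace the separate paired t tests by one linear mixed model:

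- values at months 0, 2 and 12 as repeated outcomes;
- visit and arm-by-visit effects with a common baseline mean, plus the covariates already listed;
- unstructured covariance;
- every contact aged 12 or over with at least one venous sample.

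Report the arm contrasts at months 2 and 12 with 95% confidence intervals, and keep the change t test as a sensitivity analysis.

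The cost is rewording one section and slightly more analysis work in the software already named, with no new data. The estimate will rely on a fitted covariance model and on losses being explained by the recorded earlier values, and the report should say so.
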